### 3.2 Secondary Objectives:

3.2.1 Intervention: to increase HIV testing; to identify contextual factors, facilitations and barriers associated with PrEP uptake;

3.2.2 Implementation Strategy: comprehensive economic analyses and fidelity measurements.

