(4) **Staff training**: During scheduled staff meetings, group huddles, or individual meetings, we will discuss the eSHxForm workflow with nurses, clinic managers, front desk staff, medical assistants, and other relevant clinical staff. This will allow us to troubleshoot any anticipated problems. Patients are sent a clinic reminder text message before clinic visits. Staff will encourage patients to complete the MyChart questionnaires (general history and the secondary eSHxForm) called the "eCheck-in". This best practice is being used at some clinical sites within Obgyn already but not all.

(5) **Pilot testing**: We will pilot test the eSHxForm workflow at each clinical site to determine the most effective strategies to get patient participation before the clinic visit.

After the pre-trial procedures, enrolled providers (N=42) will be randomly assigned 1:1:1 to a study arm mentioned below.

**Phase II** includes conducting the clinical trial. Patients of the enrolled provider who attend the ObGyn clinic for any preventative visit will complete an electronic sexual history form (eSHxForm) before engaging the provider. Ideally, patients will complete the eSHxForm before clinic through a message sent through the patient portal (MyChart), email, or secure text messaging. If this has not been completed, then a computer tablet will be used while the patient waits for their provider.

Patients who score low (0-3) will receive an electronic message offering a laboratory HIV test per USPSTF guidelines, only if Epic does not locate an HIV test in the record already. USPSTF recommends those 15-65 receive at least one HIV test in their lifetime. If she accepts, then an EHR alert will pop-up for the clinic staff to pend the HIV test order for the provider to discuss with the patient and discuss. The clinic staff will notify each provider when there is an HIV test order pending in the chart. Based on our preliminary data, we anticipate that the majority of our patients will fall into this category of low risk (>90-95%).

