Patients who score medium or high (4-10) will be assigned a study arm based on their provider's group. This will occur automatically via programming integrated into the EHR based on the provider and the type of scheduled visit. The score will be recorded in EHR but it will not be labeled, i.e. a number will be there but nothing about HIV or risk of HIV. This medium/high score group is whom we consider **PrEP-eligible** (e.g., *at substantial HIV risk*) and is the focus of this implementation science study. Based on our preliminary data, we anticipate that a minority of patients (5-10%) will fall into these categories of medium or high risk.

**Clinical trial arms.** The Interventions are guided by the Information-Motivation-Behavior model of behavior change (**Figure 1**).

-Arm 1 Control: standard of care

-Arm 2 Patient-level intervention: patients will be shown a 2.5-minute PrEP animation (information) and their personalized HIV risk messaging (motivation)

-Arm 3 Patient and Provider multi-level intervention: patients will be shown a 2.5-minute PrEP animation (information) and their personalized HIV risk messaging (motivation) AND providers will receive an EHR alert about their patient's personalized HIV risk messaging and a recommendation to offer PrEP. The alert will allow the provider to accept to add the required laboratory tests to start PrEP or decline altogether. Orders will have to be signed by providers but the correct laboratory tests will be ordered to save time and ensure accuracy.

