| EFFECTIVENESS                                                                                             | Number of patients who initiate PrEP (primary outcome)                                                                                                                     | Number of providers who document offering of PrEP                                                          | Patient and Providers | EHR chart review                                                                          |
|                                                                                                           |                                                                                                                                                                            | Number of PrEP prescriptions written                                                                       | Providers             | EHR discrete data element                                                                 |
|                                                                                                           | Number of patients who continue PrEP at 3-, 6-, 9- mos                                                                                                                     | Number of PrEP prescriptions written                                                                       | Providers             | EHR discrete data element                                                                 |
|                                                                                                           | Number of patients who are tested for HIV                                                                                                                                  | Number of providers who document offering of HIV test                                                      | Patient and Providers | EHR lab data for HIV testing; EHR chart review                                            |

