## 8.2 Secondary endpoints

**8.2.1** Intervention: Proportion of HIV test completion 4 weeks after clinic visit

**8.2.2** Implementation Strategy: cost-effectiveness, return on investment (ROI), budget impact, number clinics that complete assessments as intended

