## 8.5 Quantitative Analyses.

We will examine whether study randomization to the three intervention arms resulted in similar provider and patient groups by comparing patient and provider level demographics with descriptive statistics. Comparison of the primary outcome between arms will be conducted based on provider arm assignment, in accordance with intention to treat. We will use generalized linear mixed-effect models with logistic regression to examine the difference in PrEP uptake (primary outcome) across arms. To account for the relationship among primary outcomes for patients with the same provider, we will specify a random provider effect. In addition, because some patients may return over the study period and be assisted by a different provider than their initial visit, we will specify a random effect for each patient, and assume a joint multivariate normal distribution for these provider and patient random effects. We will adjust these comparisons for any demographic differences

observed between arms. We will examine the primary outcome stratified by race/ethnicity. In exploratory analyses, we will examine whether intervention effects attenuate over time, as providers and patients may become accustomed to the intervention. **Secondary Outcomes:** Similar to our methods for comparing the primary outcome between provider arms, we will also compare the rate of male partner HIV self-test completion (confirmed via text message or phone/video call) with generalized linear mixed-effect models with a provider and patient level random effects. We will use similar methods to compare the HIV test completion rates of male partner and patients who score low-risk. We will consider adjustment for factors that are imbalanced between arms in these analyses. In addition, we will also examine PrEP uptake among low-risk score patients to determine whether providers who are receiving the intervention are being influenced in their behavior more generally, or if the intervention effect is specific only to intervention patients. R (ver 4.1) will be used for analyses.

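### Section 8.5 compares HIV testing only in male partners and low-risk patients, and not in the medium/high-risk patients who receive the arm-specific interventions

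*Protocol*

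**What the plan says.** **Objective, endpoint and outcome table.** Protocol 3.2 gives the secondary intervention objective as "to increase HIV testing; to identify contextual factors, facilitations and barriers associated with PrEP uptake". Protocol 8.2.1 gives the endpoint as "Proportion of HIV test completion 4 weeks after clinic visit". Table 1 in Section 8.0 lists "Number of patients who are tested for HIV" as an effectiveness outcome, taken from EHR laboratory data. None of the three is limited by risk score, and none mentions partners.

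**Analysis.** Protocol 8.5, under secondary outcomes, begins with partners: "we will also compare the rate of male partner HIV self-test completion", to be confirmed by text, phone or video. It continues: "We will use similar methods to compare the HIV test completion rates of male partner and patients who score low-risk". It then adds PrEP uptake in low-risk patients, to see whether providers' behaviour changes beyond the intervention patients.

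**Who receives what.** Protocol Section 4 says: "Patients who score low (0-3) will receive an electronic message offering a laboratory HIV test per USPSTF guidelines", provided that no HIV test is already on record. For the others it says: "Patients who score medium or high (4-10) will be assigned a study arm". The arm descriptions follow directly: standard of care in Arm 1, animation and personal risk message in Arm 2, and the same plus a provider alert in Arm 3. Section 4 calls this medium/high group the focus of the study.

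**The concern.** An endpoint stated for all patients should be analysed where the randomised intervention acts. For HIV testing, 8.5 names two groups. One is not part of the trial. The other is not described as receiving anything that varies by arm. The group that does receive the interventions is not named.

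HIV test completion is the only intervention endpoint in 8.2. The hypothesis in 2.2 expects testing to rise, and the economic analysis in 8.6 counts incremental HIV tests for each active arm against standard of care. If the analyst follows 8.5 literally, neither has an arm comparison in treated patients behind it. If the analyst departs from 8.5, the analysis population is chosen outside the protocol's text, possibly after data have been seen.

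**Working it through.** **1. Male partners: is there anything behind the outcome?** I looked for each element that an outcome needs.

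| Element | Where it would stand | Male partners present? |
|---|---|---|
| Study population | Protocol Summary; 5.1 | No: providers, patients and staff only |
| Eligibility | 5.2, 5.3 | No |
| Self-test supply or partner contact procedure | Sections 6 and 7 | No |
| Objective | 3.1, 3.2 | No |
| Endpoint | 8.1, 8.2 | No |
| Table 1 row and data source | 8.0 | No |
| Consent or waiver | 13.5 | No: providers, patients and staff only |

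Elsewhere, partner testing or partner status appears only in the background (2.1), and partner notification appears as routine care after a positive result (10.1). The only operational detail is the confirmation route given in 8.5 itself.

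**2. Low-risk patients: does anything differ by arm?** Section 4 makes the test message depend on a score of 0-3 and no HIV test on record. Section 6.2.1 makes the staff alert depend on a low score and the patient's wish for a test. Section 13.5.2.1 repeats the recommendation for low scorers. None of the three carries an arm condition. Section 8.5 itself treats low-risk patients as lying outside the intervention group when it discusses PrEP uptake.

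**3. Medium/high-risk patients: could the interventions change testing?** Arm 3's alert lets the provider add the laboratory tests needed before PrEP (Section 4). The protocol does not list those tests. That an HIV test is among them is my reading, and 3.1.2 supports it by naming automated HIV test orders among the electronic resources. Section 8.5 gives no HIV-test comparison for this group.

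**4. Size of the groups.** Inputs are 7,800 patients a year, three years of enrolment and 5-10% scoring medium/high (8.3), and three arms with 14 providers each (8.4).

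- Patients: 7,800 × 3 = 23,400, which reproduces the protocol's figure.
- Medium/high at 5%: 0.05 × 23,400 = 1,170, which reproduces 5.1 and 8.3.
- Per arm, assuming equal patient volume: 1,170 / 3 = 390.
- Arms 2 and 3 together: 2 × 390 = 780, and 780 / 23,400 = 3.3% of all patients.
- Low-risk: 23,400 − 1,170 = 22,230, or 95%. Fewer receive the test offer, because those with a test on record do not; the protocol does not say how many.
- At the upper 10%: medium/high 2,340, of whom 1,560 are in Arms 2 and 3; low-risk 21,060.

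**5. Power.** Section 8.3 gives an uptake rate and an intra-provider correlation for PrEP uptake only. No HIV-testing rate, effect or correlation is given, so power for an HIV-test comparison cannot be derived from the document.

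**The case against.** **The endpoint is unrestricted and the SAP is not shown.** Section 8.5 never says that HIV testing will be compared only in low-risk patients, and a fuller secondary analysis could properly sit in the SAP. This limits the point. A reader might infer that the protocol rules out testing the objective in treated patients. It does not: 3.2.1, 8.2.1 and Table 1 leave room for that analysis, and the data would exist. What stands is that 8.5 is not silent. It names populations, and they do not fit the endpoint.

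**The identical low-risk offer is inferred.** No text says that the message is the same in every arm. Section 5.1 says Epic assigns each patient to an arm, without limiting this to scores of 4-10, and the schema figure and Appendix C are not visible. The inference from three places without an arm condition is reasonable, but it should not be stated as fact.

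**A low-risk comparison is not empty.** Providers are the randomised unit and are not masked (8.4), so Arm 3 providers might change their practice more widely. A reader might infer that a null result in low-risk patients would say nothing about the interventions. That goes too far, because it would bear on spill-over. It could not show the direct effect on testing.

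**The partner text may be stray wording.** This is plausible, since 8.2 lists no partner outcome. It still stands in the analysis section and must be resolved.

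**Conclusion.** The point holds as a mismatch between 8.5 and the objective, endpoint and table that it should serve. The male-partner outcomes have nothing in the protocol to support their collection. The one patient group named is not described as receiving arm-specific content. The group that is so described is left out: about 1,170 patients, about 780 of them in Arms 2 and 3, at the protocol's 5% and with equal patient volume per arm.

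The conclusion rests on the visible text. If Appendix C or the schema gives low scorers different content by arm, the part about low-risk patients would weaken. The male-partner part and the missing medium/high-risk comparison would not.

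No detectable difference should be attached to this point. Any such figure would need an invented testing rate and a design effect borrowed from PrEP uptake.

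Severity is should-fix. The primary PrEP analysis, the randomisation and the primary power statement are unaffected, and patients' HIV test results are already an EHR data source in Table 1.

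**What to change.** In Section 8.5:

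1. State that HIV test completion within 4 weeks of the visit will be compared by arm in medium/high-risk patients, with the same mixed-effects logistic model as the primary outcome.
2. Report low-risk patients separately, and label that comparison as a spill-over analysis. Together the two strata cover the unrestricted endpoint in 8.2.1.
3. Remove the male-partner outcomes. If they are intended, add the population, eligibility, self-test and contact procedures, consent, endpoint and Table 1 row that they need.
4. Make no power claim for the HIV-test comparison unless a testing rate and its source are added.

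Items 1, 2 and 4 cost only wording in the protocol, carried into the SAP, and need no new data. Removing the partner outcomes is also wording. Keeping them would mean new procedures and a new IRB submission. The change should be made before outcome data by arm are examined.

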## **8.6 Other statistical considerations.**

There is potential for significant interaction between interventions, determinants (for example, patient and provider characteristics), mechanisms (for example, motivation and skills), PrEP outcomes, and that these potential interactions likely have value for practice. It is possible that the intervention may be efficacious for some patients or providers, while not for others. In addition to our primary analysis, we will also examine who is most likely to use PrEP, since the determinants of PrEP uptake are not well-studied in this population, and whether the intervention was more effective for specific groups, focusing on differences by geographic area (zip code), patient marital status, patient insurance type, patient race and ethnicity, patient age, and patient risk score (medium vs high).

We expect differences in the rate of PrEP uptake for different providers that may depend on provider characteristics such as training or type of provider (e.g., nurse practitioner, physician), years in practice, and whether they are of the same race or gender as patients. We do not expect provider characteristics to impact trial outcomes because providers will be randomized to the intervention. However, we plan to examine the impact of provider characteristics on PrEP uptake independent of the intervention in secondary analysis, using generalized linear mixed-effect models, analogous to methods used in our primary analysis.

JHU will conduct a cost-effectiveness analysis (CEA) from the perspectives of a payer or an adopting organization (e.g., Medicaid), and using standard analytical methods recommended by the Second Panel on Cost-Effectiveness Analysis. We will measure the relative efficiency of each active intervention (i.e., patient-focused intervention and patient-focused intervention plus EHR alerts) relative to standard of care in terms of their incremental cost-effectiveness ratios (ICER), calculated as the ratio of each intervention's incremental costs to its incremental benefits (e.g., incremental new STI/HIV test, new STI/HIV case diagnosed, number of new women on PrEP), and expressed in terms of dollars per health benefits. The ICER will be compared to a payer's "opportunity cost," i.e., willingness-to-pay (WTP) threshold to determine the intervention's acceptability in terms of its efficiency in generating health benefits, and under the particular implementation strategy. An ICER below the WTP will be indicative of good value for money produced by the intervention. Additionally, we will calculate the net monetary benefit and net health benefit of the intervention.

We will conduct a ROI by calculating the intervention's benefits, that is, the monetary values to the payer (or health care sector) of positive outcomes from the intervention (e.g., cost-offsets from avoided direct medical costs, as described above), minus its costs (i.e., incremental implementation costs, as measured above), expressed as a proportion of the incremental implementation cost.

We will estimate the total budget needed to finance each intervention strategy. We will calculate the incremental costs of the intervention for all those in need in the population covered by the payer, on a "per capita" basis, per unit of time (1 year). The population in need will be estimated by multiplying the prevalence of the condition by the total number of individuals covered by the payer.

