## 5. STUDY POPULATION

### 5.1 Selection of the Study Population

**Provider eligibility:** N=42 ObGyn providers will be randomized. We chose providers as the unit of randomization to minimize contamination of the arms as many providers see patients at more than one clinic site. This will reduce the provider from being exposed to both interventions and unconsciously applying them to patients in the control arm.

**Patient eligibility:** Cisgender women of the enrolled providers aged 15-65 years scheduled in Epic for one of the following visit types: well-woman exam (annual exam), STI testing, pre-conception counseling, or contraception consult (birth control) will complete the eSHxForm. Programming in Epic will assign each patient to a study arm based on their provider's assigned study group. The age range was selected based on the United States Preventive Services Task Force (USPSTF) HIV Testing Recommendations, and PrEP FDA-approved age of 15 years. Based on preliminary clinical data, we estimate that we will have 23,400 women who will complete the eSHxForm and an estimated 5% (n=1170) will fulfill eligibility for PrEP.

**Staff eligibility:** N= 50 clinical staff who work at one of the six Obgyn clinics. These will include front desk, medical assistants, nurses, and clinic managers.

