## 8.3 Sample Size Estimate and Power.

A priori sample size calculation for the three-arm RCT was based on the expected annual patient volume across six clinics of approximately 7,800. We make the conservative assumption that 5-10% of these will score medium/high-risk on the Gyn HIV Risk Tool based on our preliminary studies, yielding 390 patients annually, with a total of 1,170 over three years of enrollment. Our estimate is conservative as we found that close to 70% of patients in one of our clinics scored medium/high, but these were adolescents and young adult women who have the highest prevalence of STIs and risk behaviors. These 1,170 patients will be seen by an expected 42 providers, where providers will be randomized to receive the potential intervention along with their patients. Given that patients using the same provider are not likely to be strongly related to each other in their choices for PrEP uptake (our co-primary outcome), we assume a low intra-provider correlation (IPC) of 0.01, with on average 28 patients per provider per year, yielding a design effect of  $1 + (28 - 1) * IPC = 1.27$ . Given these assumptions, if we estimate PrEP uptake at 6% (prelim data), we will be able to detect a difference of 9% (from 6 to 15%) between arms with 80% power. We will examine the intervention effect within specific race/ethnicity groups. We will include race and ethnicity in our minimizing of differences between arms at randomization, so we can assume that race and ethnicity will be similarly distributed across arms. Assuming we have approximately 50% non-Latinx Black patient participants (as we do for the general patient population), we expect to enroll 585 non-Latinx Black patients, allowing for 80% power to detect a difference of 6% in PrEP uptake in the standard of care arm to 15% in the intervention arms, assuming the same design effect of 1.27.

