## 8.4 Randomization and Blinding

ObGyn providers will be randomly assigned to one of three study arms based on minimization techniques developed by Pocock and Simon. This minimization approach reduces covariate imbalances by utilizing non-uniform assignment probabilities for the different arms. The study arms will be balanced over the different clinics with equal sampling rates. Providers will be randomized in equal proportions between arms (14 providers per arm). All study personnel, study analysts, and patients will be masked to group assignment. Providers will be unmasked to group assignment. New providers who join a practice after another provider has left will undergo randomization.

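### Section 8.6 sets aside provider traits it expects to drive PrEP uptake because providers are randomised; with 14 per arm they should be balanced and pre-specified as covariates

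*Protocol*

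**What the plan says.** Section 8.6 makes two statements in sequence. The first is "We expect differences in the rate of PrEP uptake for different providers that may depend on provider characteristics", with training or provider type, years in practice, and race or gender concordance with patients as examples. The second is "We do not expect provider characteristics to impact trial outcomes because providers will be randomized to the intervention". The section then leaves provider traits to a secondary analysis of uptake.

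On allocation, Section 4 says "enrolled providers (N=42) will be randomly assigned 1:1:1 to a study arm", and Section 8.4 gives 14 per arm. The method in Section 8.4 is "ObGyn providers will be randomly assigned to one of three study arms based on minimization techniques developed by Pocock and Simon". The protocol names two things to balance:

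- Clinic, in Section 8.4: "The study arms will be balanced over the different clinics with equal sampling rates".
- Race and ethnicity, in Section 8.3: "We will include race and ethnicity in our minimizing of differences between arms at randomization". In context these are the patients'.

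Section 5.1 notes that "many providers see patients at more than one clinic site".

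On analysis, Section 8.5 compares patient and provider demographics between arms descriptively, adjusts the primary comparison for demographic differences that are observed, and fits a random provider effect.

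**The concern.** PrEP uptake is the primary outcome. If uptake depends on provider type or experience, those traits bear on the trial outcome in any single allocation, whatever their average effect over hypothetical repeats. Randomisation makes imbalance a matter of chance. It does not remove it when each arm has only 14 units. Nor does it remove effect modification, which Section 8.6 itself anticipates when it says the intervention may work for some providers and not others.

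Neither of the plan's two remedies clearly reaches these traits. The named balancing factors do not include them, and clinic is not a single attribute of a provider who works at several sites. The adjustment in Section 8.5 is triggered by what is seen after allocation, and the word demographic may not cover provider type or years in practice.

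At stake are precision and the credibility of the arm comparison. This applies particularly to Arm 2 against Arm 3, the contrast in primary objective 3.1.1, for which Section 8.3 gives no separate effect size.

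**Working it through.** **Inputs from the protocol.** 42 providers in three equal arms, 42/3 = 14 per arm, which matches Section 8.4. From Section 8.3: intra-provider correlation 0.01, 28 patients per provider (1,170/42 = 27.9), design effect 1 + 27 × 0.01 = 1.27, control uptake 6%, target difference 9 points.

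**Assumptions.** The protocol gives no provider mix, so the share of providers with a trait is assumed: half, with a quarter as the alternative. Allocation is treated as simple random with equal arms, which describes a trait that the minimisation does not balance directly or through clinic. Equal patient numbers per provider are assumed, as in the 1.27.

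**1. Chance imbalance in one trait.** Let 21 of 42 providers have the trait.

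- Variance of the count in one arm: 14 × 0.25 × 28/41 = 2.39.
- Covariance between two arms: −14 × 14 × 0.25/41 = −1.20.
- SD of the difference: √(2 × 2.39 + 2 × 1.20) = 2.68 providers; 2.68/14 = 19 percentage points.

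Probabilities from the multivariate hypergeometric distribution:

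| Share with trait | Gap | A given pair of arms | Some pair of the three |
|---|---|---|---|
| 21 of 42 | at least 3/14 (21 points) | 35% | 58% |
| 21 of 42 | at least 4/14 (29 points) | 19% | 38% |
| 10 of 42 | at least 3/14 | 27% | 54% |
| 10 of 42 | at least 4/14 | 12% | 27% |

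With three independent traits each held by half of providers, a gap of at least 4/14 on one or more of them has probability 47% for a given pair and 76% for some pair.

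**2. What all provider variation does to an arm difference.**

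- Between-provider SD: √(0.01 × 0.06 × 0.94) = √0.000564 = 0.0237, or 2.4 points.
- SE of an arm difference from this source: 0.0237 × √(2/14) = 0.0090.
- 95% range: 1.96 × 0.0090 = 0.018, or ±1.8 points.
- At an assumed correlation of 0.05: SD 5.3 points, SE 2.0 points, range ±3.9 points.

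**3. The share that measured traits could account for.** Suppose one trait held by half of providers explains half of the provider variance (assumption).

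- Difference in uptake between provider groups: 2 × √(0.5 × 0.000564) = 0.034, or 3.4 points.
- Shift in an arm contrast from a 3/14 gap: 3.4 × 3/14 = 0.7 points.
- Design effect after accounting for the trait: 1 + 27 × 0.005 = 1.135, so effective sample size rises by 1.27/1.135 = 1.12, or 12%.
- At correlation 0.05: 2.35/1.675 = 1.40, or 40%.

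**The case against.** The strongest reply is that the plan already protects the comparison. Allocation is by minimisation and not by simple randomisation. Race and ethnicity are balanced as well as clinic. Provider demographics are compared and observed differences adjusted for. The random provider effect carries between-provider variance into the standard error. The ±1.8 points is the whole provider variance, which the 1.27 design effect already counts. On the assumption in step 3, a 3/14 gap moves a contrast by 0.7 points against a 9-point target. Neither Section 8.3 nor Section 8.4 says that its balancing factors are the complete list.

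Most of this stands, and it rules out several stronger readings that a reader might infer:

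- *That the protocol says provider traits cannot affect outcomes.* It says only that this is not expected.
- *That this sentence is why the traits were left out of the allocation.* No section gives it as the reason.
- *That a large imbalance is likely.* This holds across several traits and all arm pairs, not for one trait in one comparison.
- *That the test is biased.* The random provider effect argues against this.
- *That Arms 2 and 3 have no planned difference.* Section 4 gives one, the provider activity. Only a separate effect size is missing.
- *That allocation is a single event.* Section 8.4 also randomises replacement providers.

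The reply does not rescue the reasoning in Section 8.6. Minimising on other factors does not secure balance on provider type, and adjustment chosen after seeing the imbalance is weaker than adjustment fixed beforehand.

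**Conclusion.** The point holds in a limited form. The inference in Section 8.6 is unsound with 14 providers per arm, and the traits that the section itself expects to matter are neither named for balancing nor fixed as covariates. The consequence is avoidable loss of precision and face validity.

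At the plan's correlation of 0.01 the loss is modest. It would matter more if the correlation were nearer 0.05, where provider variation alone spans about ±3.9 points. The imbalance probabilities rest on the assumed trait share and on no indirect balance through clinic. The 12% and 40% gains rest on the assumption that measured traits explain half the provider variance. The change is worth making because it is cheap, not because the primary test is invalid without it.

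**What to change.** - **Section 8.6:** replace the sentence with one saying that randomisation balances provider traits in expectation only, and that named traits are handled in allocation and analysis.
- **Section 8.4:** add provider type (physician against nurse practitioner, midwife or physician assistant) to the minimisation. State the full list of factors in one place, including race and ethnicity from Section 8.3. Code a multi-site provider's clinic as the site of that provider's largest volume.
- **Section 8.5:** pre-specify provider type and years in practice as fixed terms in the primary model, in place of adjustment triggered by observed imbalance. Both should be obtainable for replacement providers when they join.
- **Optional:** balance on prior-year eligible-visit volume, with a rule for new providers who have no prior data. This is a matter of preference, since the protocol does not name volume as a driver of uptake.

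The cost is a change to the minimisation set-up, a volume query in Epic to assign multi-site providers to a clinic, and one or two extra model terms. The downside is slightly looser balance on each minimisation factor.
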